**Figure 3 figure3:**
[figure not shown]
Study procedures. NCI: National Cancer Institute; NCORP: National Cancer Institute Community Oncology Research Program.

After enrollment, participants will be invited to complete the web-based baseline assessment via REDCap (step 5). On completion of the baseline assessment, participants will be automatically randomized to 1 of the 16 study conditions via REDCap (step 6). Block randomization will be used to help maintain balance across conditions, with varying block sizes of 16, 32, and 48 [44,45]. A participant’s randomized condition will not be revealed to the local NCORP study staff; only the UVA research coordinator (who implements participants’ conditions in the SHINE intervention system) and a WF NCORP RB data manager will have access to participants’ randomized condition information. Participants cannot be blinded to their condition. Participants will receive a welcome email directing them to set a password and log into their SHINE program (ie, the set of components assigned to them in their randomized condition; step 7).

After baseline, participants will be asked to complete their SHINE program within the following 12 weeks and to complete follow-up assessments through REDCap at 12 and 24 weeks (steps 8 and 9). A protocol of stepped reminder emails via REDCap and contacts by NCORP site research staff will encourage participants to complete all study assessments.

### Intervention

Intervention components are delivered fully automated as a *Core*, or lesson, of content. Components (and component levels) to be tested are (1) education about the influence of breast cancer on sexual health, either with limited information in a static web page format in the Sexual Health Essentials-Standard Core or more comprehensive information through an interactive web program in the Sexual Health Essentials-Enhanced Core; (2) communication skills training for discussing sexual concerns with one’s health care team in the Health Care Discussions Core; (3) communication skills training for discussing sexual concerns with one’s intimate partner in the Partner Conversations Core; and (4) intimacy promotion skills training in the Intimacy Insights Core. All participants will receive 1 of 2 Sexual Health Essentials Cores (ie, standard [component level=low] or enhanced [component level=high]) given that survivorship care guidelines recommend that all survivors receive education about the influence of cancer treatment on sexual health [21]. For the 3 remaining components, participants will either receive the Core (component level=on) or not receive the Core (component level=off; see Figure 2 for factorial design and Multimedia Appendix 2 for additional Core details).

The Sexual Health Essentials-Enhanced, Health Care Discussions, Partner Conversations, and Intimacy Enhancement Cores each deliver content as stand-alone, web-based programs. These Cores were developed following the Model for Internet Interventions [46] and user-centered design practices to be highly engaging, using interactive elements, audiovisuals, and tailoring. Cores were developed with a team of software engineers and consultants in user interface, user experience, and instructional design. Core content was refined through iterative feedback from survivors of breast cancer. The Sexual Health Essentials-Standard Core provides education via a traditional web page with no tailoring or interactive elements.

Cores take about 20-45 minutes to complete, which participants may do at their convenience and own pace (ie, Cores do not need to be completed in 1 sitting). Participants must complete their Sexual Health Essentials Core (enhanced or standard) before any remaining Cores in their randomized condition are made available. These remaining Cores may be completed in any order. Completed Cores may be revisited and reviewed as often as desired. While technical support is available from the UVA research coordinator, no clinical support will be provided. All Cores were written to an eighth-grade reading level (Flesch-Kincaid Grade Level) [47] or lower.

Participants will access their SHINE program via a password-protected website by computer, tablet, or smartphone. Participants will be monitored by the UVA research coordinator to ensure that they set up a password and can successfully log into the program. The goal of this monitoring is to ensure that the participants can access the intervention. Participants who do not complete their first log-in within a day of receiving the welcome email will receive daily automated reminder emails from the program. If the participant still has not logged in after 3 automated reminder emails, contacts will escalate to reminders by phone call and personal email by the UVA research coordinator and then by the local NCORP site research staff.

There are also automated email prompts to support participant engagement with the SHINE program after participants have successfully logged into the program. Participants who do not initiate Cores within 3 days of initial access will receive a reminder prompt. All participants will receive weekly progress emails regarding their progress through each of their assigned Cores. After participants complete their assigned SHINE program, email prompts will remind them that they may continue to access their SHINE program and review their Cores as desired.

### Measures

#### Overview

Study measures are summarized in Table 2. REDCap surveys require all items to be answered to limit missing data; however, participants may select a “refuse to answer” response for any item. Medical record data on enrolled survivors are collected by participating NCORP site research staff using a standardized medical record data extraction form in REDCap.

**Table 2 table2:** Study measures.

Variable or construct			Measurement		Time point (weeks)				
					0 (baseline)		12		24
**Screening**									
	Cancer diagnosis and treatment; age	Medical record extraction							
	Sex and gender; relationship status; cancer-related sexual concerns; access to internet and email; serious mental illness; current therapy; and current pregnancy	Self-reported web-based screening questionnaire							
**Sample characteristics**									
	Demographics (eg, race, ethnicity, education, household income, sexual orientation, and partner gender)	Self-reported		✓					
	Medical history (eg, diagnosis, treatment type and dates, and other cancer history)	Medical record extraction		✓				✓	
	Recent sexual experiences, changes in partner status	Patient-Reported Outcomes Measurement Information System sexual functioning screener		✓		✓		✓	
**Sexual morbidity outcomes**									
	Sexual distress (primary)	Female Sexual Distress Scale-Desire, Arousal, Orgasm		✓		✓		✓	
	Sexual functioning (secondary)	Female Sexual Function Index		✓		✓		✓	
**Mediators**									
	Sexual functioning knowledge	4-item knowledge perception; 8-item knowledge quiz		✓		✓		✓	
	Sexual communication self-efficacy with clinicians	2-item confidence to raise and discuss sexual concerns		✓		✓		✓	
	Sexual communication self-efficacy with partner	Self-Efficacy to Communicate about Sex and Intimacy scale		✓		✓		✓	
	Emotional intimacy with their partner	Personal Assessment of Intimacy in Relationships—emotional intimacy subscale		✓		✓		✓	
**Moderators**									
	Menopause status	Self-reported		✓					
	Adjuvant endocrine therapy use	Medical record extraction		✓					
	Time since primary breast cancer treatment	Medical record extraction		✓					
	Psychological distress	Patient Health Questionnaire-4		✓		✓		✓	
	Relationship duration	Self-reported		✓					
	Relationship satisfaction	Relationship Assessment Scale		✓		✓		✓	
**Engagement and acceptability**									
	Engagement	Log-ins, Core completion (recorded by the intervention platform throughout the 24-week study period)							
	Satisfaction	Client Satisfaction Questionnaire-8				✓			
	Usability	Internet Intervention Utility Questionnaire				✓			

#### Sexual Morbidity Outcomes

Two outcomes will be evaluated to determine the optimal combination of intervention components: the Female Sexual Distress Scale–Desire, Arousal, Orgasm (FSDS-DAO [48,49]; primary outcome) and the Female Sexual Function Index (FSFI [50-52]; secondary outcome). These measures will be assessed at all 3 time points (ie, baseline, 12-week, and 24-week assessments); the primary evaluation is change between baseline and 24-week assessments.

The FSDS-DAO measures sexual distress among women and will be the primary outcome of the intervention optimization decision-making process. It has established reliability, construct and discriminant validity, and sensitivity to treatment-related changes [48,49]. Participants will rate 15 items on a 5-point Likert scale from 0 (never) to 4 (always). Total sum scores range from 0 to 60, with higher scores reflecting greater sexual distress.

The FSFI measures sexual functioning among women. It also has established reliability, construct and discriminant validity, and sensitivity to treatment-related changes [50-52]. Scores will only be evaluated from women who report having sexual activity within the past 4 weeks, as recommended [53]. Participants rate 19 items on a 5- or 6-point Likert scale from 0 (eg, no sexual activity) or 1 (eg, almost never or never) to 5 (eg, almost always or always). To compute a total score, summed scores of each of the 6 domains (desire, arousal, lubrication, orgasm, satisfaction, and pain) are scaled to a maximum score of 6, which are in turn summed for the total score. Total scores range from 2 to 30, with higher scores representing better sexual functioning and a total score of ≤26.0 suggestive of clinically relevant sexual dysfunction.

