#### Sample Size and Power Analysis

This factorial trial has been powered to detect a small-to-medium effect size (ie, Cohen *d*=0.30) of intervention components on sexual morbidity outcomes. This represents the smallest effect size that the study team determines would offset the required resources of an intervention component to be delivered to and completed by participants in an optimized intervention. Determined using the MOST R package [60] *FactorialPowerPlan* function (R version 3.6.2; R Foundation for Statistical Computing), 247 survivors of breast cancer would be needed to detect Cohen *d*=0.30 of change in sexual distress from baseline to 24-week assessment (measured by FSDS-DAO) at 80% power with α=.05 for all main effects and interaction effects of the intervention components. In a factorial experimental design with only 2 levels per factor, the power to detect main effects and interaction effects is equal [39,61]. This power analysis assumes a pretest-posttest correlation in sexual distress of *r*=0.65, which is supported by data from the investigators’ prior research (Female Sexual Distress Scale pretest-posttest *r*=0.73; N=28) [32] and by Female Sexual Distress Scale validation data (pretest-posttest *r*=0.62; N=318) [49]. The effect size of Cohen *d*=0.30 is reasonable to expect from intervention components, given that prior randomized controlled trials of interventions containing the components demonstrated large effects on sexual distress relative to control (Cohen *d*=0.87 and Cohen *d*=0.59) [28,32]. Conservatively accounting for an estimated 20% attrition (based on the investigators’ past trials) [32,42,62] and rounding up to achieve a balanced number of participants per condition, 320 survivors will be randomized in the trial (247/0.80=309 rounded to a total N=320, for n=20 per each of the 16 factorial conditions).

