#### Primary Objective Analyses

The primary objective of this study is to identify the most efficient intervention package that is expected to produce the greatest benefit to survivors’ sexual health with the fewest (and least-intensive) intervention components. This objective will be achieved using an “all-active components” optimization criterion to guide a decision-making process with systematic data analysis [39]. The main and interaction effects of components will be computed using a generalized linear model (GLM) approach to ANOVA with effect coding to compare the average change in sexual morbidity aggregated across experimental conditions [66].

A model will be conducted for effects on sexual distress, measured by the FSDS-DAO; this model will be prioritized for the intervention optimization decision-making process. First, only components (and component levels) that have a beneficial independent effect (ie, a small-to-moderate positive main effect [Cohen *d≥*0.3]) on sexual distress will be provisionally included. Next, these provisional decisions will be reviewed by examining component interaction effects. Components will be considered for addition to the intervention package if they have important (ie, Cohen *d≥*0.3) synergistic effects, meaning they amplify the benefit of another component in the package. Components will be considered for removal from the package if they have important (ie, Cohen *d≥*0.3) antagonistic effects, meaning they reduce the benefit of another component in the package. Decisions will be informed by computing parsimonious prediction models for outcomes from both the main and interaction effects of the included components [39].

A subsequent model will be conducted for sexual functioning among women reporting sexual activity within the past 4 weeks, measured by the FSFI. Model results will be compared between sexual distress (full population) and sexual functioning (sexually active population only). Components (and component levels) provisionally included based on the sexual distress model findings may be removed if there is a substantial negative effect on sexual function. While discrepant or antagonistic results between the sexual distress and sexual functioning models are possible, they are unlikely, given that FSDS-DAO and FSFI total scores have been found to be highly correlated (*r=*–0.65 [49]).

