#### Mediation

An established strategy using structural equation modeling for testing mediation in a factorial experiment will be followed [67]. The mediation effects of components on both sexual distress and sexual functioning will be evaluated within a single model. Mediation hypotheses will be supported if (1) changes in the mediators influence the change in sexual morbidity, (2) intervention components influence the change in the mediators, and (3) changes in the mediators account for the relation between intervention components and changes in sexual morbidity.

In an optimization trial design, mediation analyses are critical both when components produce a positive effect and when there are null findings [68]*.* If there are null findings of components on primary outcomes, mediation analyses support the next research steps by determining where a breakdown may have occurred. For instance, a hypothesized mediator may influence the outcome, but the component did not adequately influence the mediator. This result would suggest that intervention revisions would be needed to better target the mediator. Mediator analyses are also critical to refining the study’s conceptual model.

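### The FSFI contrast that can remove a component is limited to women who are sexually active, so it is not fully a randomised comparison, and the stated power does not cover it

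*Protocol article*

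**What the plan says.** Sexual Morbidity Outcomes restricts the FSFI: "Scores will only be evaluated from women who report having sexual activity within the past 4 weeks, as recommended [53". For both outcome scales, "the primary evaluation is change between baseline and 24-week assessments".

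Primary Objective Analyses carries the restriction into the model: "A subsequent model will be conducted for sexual functioning among women reporting sexual activity within the past 4 weeks, measured by the FSFI". The two scales are then set against each other in different populations: "Model results will be compared between sexual distress (full population) and sexual functioning (sexually active population only". The FSFI has decision weight, because components provisionally included on the distress result "may be removed if there is a substantial negative effect on sexual function". The article expects conflict between the scales to be unlikely because they correlate at r=-0.65.

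Sample Size and Power Analysis describes the trial as "powered to detect a small-to-medium effect size (ie, Cohen *d*=0.30) of intervention components on sexual morbidity outcomes". The calculation that follows concerns FSDS-DAO change only.

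Sexual activity is not an eligibility criterion (Table 1 and Participants). Table 2 lists recent sexual experiences as collected at baseline, 12 and 24 weeks. The sensitivity analyses in the Data Analysis Plan overview address attrition and Core completion, not inactivity.

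**The concern.** A 24-week change score needs a 24-week score. Under the scoring rule, a woman with no recent sexual activity at week 24 does not contribute one. Whether she is active then is observed after randomisation, and one component is "intimacy promotion skills training in the Intimacy Insights Core"; another trains conversations with the partner. If such a component alters who is sexually active, the women scored with the component on and those scored with it off are selected differently, and the difference in FSFI change mixes a treatment effect with that selection.

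In one plausible case, a component helps women with poorer function to stay or become active. Their scores then enter only the group with the component on, and the component looks worse on the FSFI than it is. The product of this trial is a decision about which components to keep, and the article lets this contrast overturn an inclusion made on distress. The stated correlation between the scales does not address selection, and neither do the listed sensitivity analyses.

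Separately, the smaller FSFI set has less power than the sample-size section suggests for sexual morbidity outcomes, a term the article uses for both scales.

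**Working it through.** **1. Reproducing the planned sample size.** Inputs from Sample Size and Power Analysis: d=0.30, r=0.65, alpha .05 (two-sided, from the overview), power 80%.
- SD of a change score in units of the raw SD: √(2(1−0.65)) = √0.70 = 0.837.
- Normal approximation: N = 4 × (1.960+0.842)² × 0.70/0.30² = 244.2, i.e. 123 per level, 246 in total.
- Noncentral t: noncentrality (0.30/0.837) × √N/2 with N−16 degrees of freedom. Power is 0.7996 at N=246 and 0.801 at N=247.
- 247/0.80 = 308.75, so 309; the next multiple of 16 is 320.

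The stated 247, 309 and 320 are confirmed. They apply to FSDS-DAO change in all retained women. With 20% attrition, 0.80 × 320 = 256 are retained.

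**2. FSFI power in the subset.** The article gives no share of women who will be sexually active, so the shares below are assumptions. It also gives no pretest-posttest correlation for the FSFI, so r=0.65 is assumed to carry over. Same formula, d=0.30:

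| Share of 256 evaluable | n | Noncentrality | Power | Effect detectable at 80% power |
|---|---|---|---|---|
| 80% | 204 | 2.56 | 72% | 0.33 |
| 70% | 179 | 2.40 | 66% | 0.35 |
| 60% | 153 | 2.22 | 60% | 0.38 |
| 50% | 128 | 2.03 | 52% | 0.41 |

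**3. Size of the selection bias.** Simulation of 4 million women: baseline and week-24 function correlated 0.65; no true component effect on function; activity at week 24 correlated 0.3, 0.5 or 0.7 with week-24 function; the component changes only the share active. Contrast in FSFI change (on minus off, raw SD units) among women active at week 24:

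| Share active, off to on | Correlation 0.3 | 0.5 | 0.7 |
|---|---|---|---|
| 60% to 60% | 0.00 | 0.00 | 0.00 |
| 60% to 70% | -0.015 | -0.026 | -0.035 |
| 75% to 85% | -0.015 | -0.026 | -0.036 |
| 50% to 70% | -0.03 | -0.05 | -0.07 |

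Requiring activity at baseline as well changes little: about -0.04 at most in the 60% to 70% and 75% to 85% rows, and about -0.08 in the last row.

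**4. Effect on a removal decision.** The article gives no figure for a substantial negative effect. As an assumption, borrow the 0.3 it uses for important interaction effects. With 204 evaluable women the standard error is 2 × 0.837/√204 = 0.117. With a true FSFI effect of zero, the chance of an estimate below -0.30 is 0.5% without bias and 1.2% with a bias of -0.035. With 128 evaluable women (standard error 0.148) the two figures are 2.1% and 3.7%.

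**The case against.** The strongest reply is that the bias is too small to matter. The FSFI is secondary, the distress model has priority, removal is discretionary, and the restriction to active women follows a cited scoring recommendation. This largely stands as to size. It does not make the contrast a randomised one: a rule about when a score is interpretable does not settle how component levels should be compared.

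Several stronger readings are tempting, and the document does not support them.
- **A larger bias.** A reader might apply the extra women's lower score directly. In the 75% to 85% case, -(0.10/0.85) × 0.5, 0.8 or 1.0 SD gives -0.06, -0.09 or -0.12 SD. But the endpoint is change, and women with worse week-24 function also tended to be worse at baseline. With r=0.65, about 1−0.65 = 0.35 of a level difference reaches the change score, which gives about -0.02, -0.03 or -0.04 SD, in line with the simulation.
- **A known direction.** A reader might infer that the FSFI result is biased against components that raise activity. That needs an effect on activity and newly active women whose change is worse. The article reports neither. If a component instead helped women with pain to decline unwanted activity, the sign could reverse.
- **Activity as an intended benefit.** The stated targets are distress and functioning, acting through knowledge, self-efficacy and emotional intimacy. More frequent activity is not among them.
- **A flawed mediation model.** The article says "The mediation effects of components on both sexual distress and sexual functioning will be evaluated within a single model". A reader might infer that inactive women must be dropped from the distress part or treated as missing at random. The article does not say how an unscored FSFI is handled, and such detail commonly sits in a fuller document.

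It is also fair to say that the restriction at follow-up is inferred: the article says only the past 4 weeks. The inference follows from the 24-week change endpoint. On power, the sentences after the opening claim do specify FSDS-DAO change, so the defect is loose wording in the claim and not a wrong calculation.

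**Conclusion.** The point holds in a limited form. For the week-24 score, the FSFI set is defined by a state measured after randomisation that the components could plausibly change. The contrast is therefore not fully randomised, and no stated analysis examines this, although the result may remove a component that benefits distress.

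The bias is zero if a component leaves activity unchanged. It is about -0.015 to -0.04 SD in the 60% to 70% and 75% to 85% scenarios, and about -0.07 SD (-0.08 if baseline activity is also required) for 50% to 70%. These figures assume r=0.65, no true FSFI effect and an activity-function correlation of 0.3 to 0.7. They are small against d=0.30, so a wrongful removal would come mainly from sampling error in a smaller set, with bias adding a little.

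The power claim holds for FSDS-DAO only. FSFI power is 52% to 72% if 50% to 80% of completers are evaluable. The change is worth making, but nothing here threatens the primary outcome, its sample size or its analysis.

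**What to change.** 1. Analyse sexual activity in the past 4 weeks at 24 weeks by component, in all randomised women. The data are already collected at that visit.
2. Label the active-only FSFI contrast as supportive, and do not remove a component on it alone. Require that the negative effect is not explained by a difference in activity between component levels, and that it persists in a sensitivity analysis that keeps women inactive at 24 weeks. The instrument's own 0 codes for no sexual activity are one way to do this. The plan should acknowledge that they mix inactivity with dysfunction, so this analysis checks the active-only result and does not replace it.
3. Restate the power claim as applying to FSDS-DAO change only.

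The cost is some rewording, one or two extra models on existing data, and a less favourable power statement for the FSFI.
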